## Abstract

Supplemental Digital Content is available in the text

## Introduction

1

Peptic ulcer disease (PUD) is a common digestive system disease that mostly involves the stomach and duodenum, corresponding to a gastric ulcer (GU) and a duodenal ulcer (DU). PUD may occur at any age, but more than half of patients are diagnosed at an age of 30 to 49 years.^[1]^ The global annual incidence of PUD has been estimated to be 0.10% to 0.19% based on physician diagnosis, with an annual prevalence ranging from 2.6% to 4.1%.^[2]^ PUD is a major problem in China, in which the prevalence was up to 17.2% in 2010.^[3]^ The pathogenesis of PUD is chronic damage to the gastroduodenal mucosa, which is mainly attributed to *Helicobacter pylori* (*H pylori*) infection and the use of nonsteroidal anti-inflammatory drugs (NSAIDs)^[4]^; 72.2% of *H pylori*-positive patients and 25% of patients with long-term NSAID use ultimately develop PUD.^[3,5]^

The typical symptoms of PUD are chronic, rhythmic, and periodic upper abdominal pain, as well as distension, belching, and inappetence.^[6]^ PUD can progress to severe complications, including bleeding, perforation, pyloric stenosis, and even cancerization, which may have life-threatening outcomes.^[7]^ Routine treatment of PUD involves a combination of *H pylori* eradication, acid suppression (eg, proton pump inhibitors [PPIs]), and gastric mucosa protection (eg, bismuth agents).^[4]^ This regimen shows definite efficacy, with an ulcer healing rate >90%.^[8]^ However, there are still some concerns with the routine treatment. Gastrointestinal symptoms generally improve significantly after treatment, but systemic symptoms (such as weakness and fatigue) can persist.^[9]^ Moreover, PUD relapse is not uncommon in patients who fail to eradicate *H pylori* and exhibit poor ulcer healing.^[10]^

In China, combinations with traditional Chinese medicine (TCM) have become an important complement to prevent and solve the above conditions.^[11]^ A number of animal and human studies have shown that TCM therapies, such as Chinese herbal medicine and acupuncture, have anti-ulcer effects and can reduce the recurrence of ulcers.^[12–17]^ In TCM theory, most cases of PUD can be classified as spleen qi deficiency (SQD) syndrome, in which the patient's spleen (an abstract organ responsible for transporting and transforming food and water that differs from the organ in Western medicine) and qi (a kind of abstract energy that sustains life) are weakened by disease to the point that are unable to function normally, resulting in a range of gastrointestinal and systemic symptoms.^[18]^ Therefore, the TCM treatment of SQD syndrome emphasizes invigorating spleen and replenishing qi to improve immunity and self-healing, and integrated TCM and routine treatments are expected to have greater efficacy against PUD.

Shen Ling Bai Zhu San is a classic TCM formula originally documented in the Song Dynasty (1102 AD). More than 3000 years of ancient experience has shown that Shen Ling Bai Zhu San has the functions of invigorating spleen and replenishing qi and can be used to treat PUD.^[19]^ Animal studies have shown that Shen Ling Bai Zhu San regulates absorption, mucosal ultrastructure, and the flora balance in the gastrointestinal tract to improve the ability to self-repair ulcers.^[20,21]^ However, there is a lack of high-quality randomized controlled trial (RCT) evidence on the efficacy and safety of this formula for PUD. Moreover, the powder preparation of Shen Ling Bai Zhu San is difficult to take and tastes bad, which is disadvantageous for the long-term management of PUD.

Hou Gu Mi Xi (HGMX), a dietary TCM formula modified from Shen Ling Bai Zhu San, was developed in 2016. HGMX replaces Atractylodes (*Baizhu*), the only component in Shen Ling Bai Zhu San forbidden to use as food according to the regulations in China, with orange peel (*Jupi*) and is made into cornmeal with japonica rice and oats to improve patient compliance. As a result, HGMX is composed of 10 dietary herbs: ginseng (*Renshen*), tuckahoe (*Fuling*), coixenolide (*Yiyiren*), Chinese yam (*Shanyao*), lotus seed (*Lianzi*), Amomum (*Sharen*), Platycodon (*Jiegen*), white hyacinth bean (*Baibiandou*), liquorice (*Gancao*), and orange peel. In this formula, ginseng and tuckahoe play roles in invigorating qi and nourishing spleen; coixenolide, Chinese yam, lotus seed, and Amomum help improve the effects of ginseng and tuckahoe; and Platycodon, white hyacinth bean, liquorice and orange peel assist in promoting lung qi and regulating the waterway to improve the absorption of the herbs. The combination of these dietary herbs is expected to be efficacious at improving immunity and ulcer healing. In addition, HGMX should have a good safety profile because of its dietary property, and no adverse events (AEs) related to HGMX have been reported in the 3 years of post-market safety monitoring.

Therefore, we hypothesize that HGMX, in combination with routine treatments, will improve ulcer healing, increase the *H pylori* eradication rate, and reduce the recurrence rate in patients with PUD, with a good safety profile and good patient compliance. To verify this hypothesis, we plan to conduct a RCT in 11 tertiary hospitals.

## Methods and analysis

2

This study is a multicenter, randomized, double-blind trial. The protocol was registered at Clinicaltrials.gov (Number: NCT03320538) on October 25, 2017, and we report the protocol according to the Standard Protocol Items: Recommendations for Interventional Trials (SPIRIT) criteria.

### Site and participant recruitment

2.1

The participants will be enrolled from 11 hospitals in 3 cities in Jiangxi Province: the First Affiliated Hospital of Nanchang University, the Second Affiliated Hospital of Nanchang University, the Third Affiliated Hospital of Nanchang University, Jiangxi Hospital of Traditional Chinese Medicine, Nanchang Hongdu Hospital of Traditional Chinese Medicine, Nanchang Hospital of Integrated Traditional Chinese and Western Medicine, The Nanchang Third Hospital, Xinyu People's Hospital, Xinyu Hospital of Traditional Chinese Medicine, Jiujiang No.1 People's Hospital, and Jiujiang Hospital of Traditional Chinese Medicine. Trial enrolment will be advertised through oral promotion by researchers, hospital posters, and web page advertising. The recruitment was started at July 10, 2017 and is expected to be completed in July 2020.

### Patient screening

2.2

Patients will be deemed eligible after screening according to the inclusion and exclusion criteria.

#### Inclusion criteria

2.2.1

1.Diagnosed with GU or DU by endoscopy and ulcer area from 0.3 to 1.0 cm^2^ with no indications of bleeding or perforation.2.Diagnosed with SQD according to the criteria in the Consensus on Integrated Traditional Chinese and Western Medicine, as follows:Main spleen deficiency (SD) symptoms: poor appetite; stomach or abdominal distention; loose stools or diarrhea.Main qi deficiency (QD) symptoms: physical fatigue and weakness; mental fatigue and taciturnity.Secondary symptoms: loss of taste or hypodipsia; stomach or abdominal pain; stomach tightness; nausea or vomiting; abnormal bowel sounds; lean or puffiness; sallow complexion; powerless defecation; facial or limb oedema.Tongue symptoms: pale, swollen, or scalloped tongue with a thin, white coating.Patients will be diagnosed with SQD if they meet: 2 main SD symptoms + 2 main QD symptoms; 2 main SD symptoms + 1 main QD symptom + 1 tongue symptom; or 1 main SD symptom + 1 main QD symptom + 2 secondary symptoms + 1 tongue symptom.3.Aged from 18 to 70 years.

#### Exclusion criteria

2.2.2

1.Complex peptic ulcer (ie, simultaneous GU and DU).2.History of ulcer complications (eg, bleeding, perforation, pyloric stenosis, and precancerous lesions).3.Indications of ulcer complications, including bleeding and perforation (Forrest stage I, IIa or IIb; positive stool occult blood; or ulcer area >1 cm^2^).4.History of use of NSAIDs, theophylline, oral antibiotics, potassium supplements, or any intervention for PUD within the last 3 months.5.Pregnant, breastfeeding, or planning to become pregnant within 2 years.6.Allergic to any trial interventions.7.Impaired liver or renal function, indicated by total bilirubin >35 μmol/L, alanine transaminase >2× upper limit of normal (ULN), aspartate aminotransferase >2× ULN, or serum creatinine >ULN.8.Other severe diseases (e.g., severe mental disorders and cancer).9.Unwilling to provide personal information.

### Randomization and blinding

2.3

Patients who pass the eligibility assessment will be randomly and proportionally divided into four groups: Group A, B, C, and D. We generated a block randomization sequence using Microsoft Excel that was saved as enciphered data. For allocation concealment, we will adopt centralized random assignment. Independent researchers who do not participate in trial procedures other than the randomization process will recode the random sequence into continuous numbers and label the boxes of trial samples. Samples will be allocated sequentially to participants. In this way, no one will know the group into which the next participant will be assigned.

This trial will have 3 intervention periods: standard treatment period, maintenance treatment period, and recuperation treatment period. The standard treatment period will be open-label. During the maintenance and recuperation treatment period, the clinicians, patients, outcome assessors, and data collectors will be blinded in terms of the assignment of HGMX or placebo but the administration of rabeprazole will be open-label. Except in instances of a severe AE, all the participants, medical providers, data collectors, and outcome reviewers will strictly adhere to the blinded de∗sign until the trial has been completed. In addition, an independent committee will supervise the allocation concealment and blinding, and if blinding is violated, the corresponding patient will be excluded. Figure 1 gives an overview of the study design and procedures.

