#### Maintenance treatment period (weeks 3 to 6)

2.4.2

The patients in the 4 groups will receive the following intervention for 4 weeks as maintenance treatment to further facilitate ulcer healing.

1.Group A: HGMX 30 g b.i.d.2.Group B: HGMX placebo 30 g b.i.d.3.Group C: HGMX 30 g b.i.d. + rabeprazole 10 mg q.d.4.Group D: HGMX placebo 30 g b.i.d. + rabeprazole 10 mg q.d.

HGMX is an oatmeal-like solid food (eaten dry or mixed with a liquid) that contains 10.1 g dietary herb material per 30 g. Table 1 presents the components of HGMX in detail. Compared with HGMX, the placebo looks the same (such as label, color and mass) but has minor differences in taste and smell that are hard to differentiate. HGMX and placebo are produced by Jiangzhong Pharmaceutical (group) Co., Ltd., and rabeprazole is produced by Shanghai Xinyi Pharmaceutical Corp. Ltd.

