### Data management

2.8

Data collection and management will be carried out by a collaboration of research associates, coordinators and clinicians. All the investigators will undergo standard operating procedure (SOP) training based on the study protocol. During the trial, subject recruitment, intervention, follow-up, data collection and data management will be performed in strict accordance with the SOPs.

The clinicians will be responsible for the baseline and outcome examinations, including SQD symptom assessments, biological sample collections, and laboratory examinations. All these data will be entered on pilot-tested case report forms. The research coordinators will be student volunteers from Jiangxi University of Traditional Chinese Medicine and will be responsible for contacting patients and helping with communication between patients and doctors. We will assign to each study center a research associate selected from researchers at Jiangxi University of Traditional Chinese Medicine who will be responsible for monitoring the follow-up process, standard performance, patient compliance, and completeness of data collection. We will develop a specialized computer system for data entry that will support data query and verification. Once verified, data will be locked and accessible to only data analysts during the data analysis period. In special cases and emergency conditions, such as SAEs, the database will be temporarily accessible, and data for the corresponding participant will be unblinded.

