### Data analysis

2.10

The primary outcome data will be analyzed using the intention-to-treat population, in which all patients will be maintained in their initial group assignment regardless of compliance and contamination, and missing data will be imputed using the last observation carried forward method. Meanwhile, we will also conduct a sensitivity analysis with the per-protocol population. The safety outcomes will be analyzed using a safety population including all participants who received treatment at least once. Mid-term and final data analyses will be performed at the end of week 52 and 104, respectively.

Normality will be detected using the Kolmogorov-Smirnov method. Normal continuous variables will be described using the mean and standard deviation and compared using a *t* test or analysis of variance. Non-normal continuous variables will be described using the median and interquartile range and analyzed with the Mann–Whitney *U* test. Categorical variables will be presented as the frequency and percentage and compared using Pearson *χ*^2^ test. The boundary of significance for the *P* value will be .05, which will be adjusted using the O’Brien & Fleming method for multiple comparisons.

According to our factorial design, we will explore whether there exists an interaction between HGMX and rabeprazole. If there are no significant interaction effects, we will compare the main effects of HGMX and rabeprazole. In addition, we will perform subgroup analysis stratified by type of PUD (GU vs. DU) and *H pylori* infection status (yes vs no). All statistical analyses will be conducted in Stata v14.0 software.

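### The rule that a patient whose blinding is violated will be excluded does not say from what, and must be reconciled with the intention-to-treat analysis and the withdrawal list

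*Protocol article*

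**What the plan says.** Section 2.3 (Randomization and blinding) has an independent committee oversee concealment and blinding and adds that "if blinding is violated, the corresponding patient will be excluded". The sentence does not say whether the exclusion is from treatment, follow-up, the per-protocol set or every analysis.

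The same section states when blinding applies: "During the maintenance and recuperation treatment period, the clinicians, patients, outcome assessors, and data collectors will be blinded" as to HGMX or placebo. Sections 2.4.2 and 2.4.3 place these periods at weeks 3 to 6 and 7 to 52. Section 2.3 also allows one exception to the blinding, which is otherwise to be kept to the end of the study: "Except in instances of a severe AE, all the participants, medical providers, data collectors, and outcome reviewers will strictly adhere to the blinded".

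Section 2.10 (Data analysis) says: "The primary outcome data will be analyzed using the intention-to-treat population", and defines that population so that "all patients will be maintained in their initial group assignment regardless of compliance and contamination". Missing data are filled by last observation carried forward. The per-protocol population serves a sensitivity analysis. The safety population is everyone treated at least once. None of these definitions makes an exception for unblinding.

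Section 2.7 (Discontinuation and withdrawal) lists five reasons for leaving the trial. Violated blinding is not one of them.

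Section 2.4.2 says that the placebo "has minor differences in taste and smell that are hard to differentiate".

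**The concern.** An intention-to-treat comparison is protected by randomisation because nothing that happens afterwards decides who is counted. A rule that removes patients when their blinding fails is a post-randomisation selection rule, and blinding can fail for reasons connected with the arm or the response. A patient may notice a taste or smell, or may improve or fail to improve in a way that reveals the allocation. If such patients leave the primary analysis, the remaining groups are no longer the randomised groups. If they leave follow-up instead, outcomes that could have been observed are replaced by carried-forward values. The unresolved wording therefore affects who contributes observed data to the primary comparison.

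**Working it through.** **1. The provisions side by side**

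| Section | Provision | Violated blinding mentioned? |
|---|---|---|
| 2.3 | Patient is excluded, object not stated | Yes |
| 2.7 | Five withdrawal reasons | No |
| 2.10, intention to treat | All patients kept in assigned group | No |
| 2.10, per-protocol | Sensitivity analysis only | No |
| 2.10, safety | All treated at least once | No |

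**2. The possible readings**

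- *Excluded from analysis.* This conflicts directly with the intention-to-treat definition in 2.10 and, if applied to safety, with the safety population.
- *Excluded from follow-up.* The patient could still be counted, but with missing outcomes filled by last observation carried forward. By the text of section 2.6, the first follow-up gastroscopy is at week 12. A patient removed between weeks 3 and 12 would have only the baseline endoscopic grade to carry forward.
- *Excluded from the per-protocol set only.* This would be harmless, but nothing in 2.3 or 2.10 says so.

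**3. Timing.** Blinding to HGMX or placebo covers weeks 3 to 52, so any violation comes after randomisation.

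**4. Illustration at the planned effect (exclusion from analysis)**

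Inputs from section 2.9: 0.85 for the two HGMX groups, 0.65 for the two placebo groups, 90 per group, hence 180 against 180. Assumption not in the article: 5% excluded per arm, 0.05 × 180 = 9.

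- No exclusion: 153/180 − 117/180 = 0.850 − 0.650 = 20.0 points.
- The 9 HGMX exclusions all responders and the 9 placebo exclusions all non-responders: 144/171 − 117/171 = 0.842 − 0.684 = 15.8 points.
- The reverse: 153/171 − 108/171 = 0.895 − 0.632 = 26.3 points.
- Exclusions unrelated to response: expected difference 20 points.

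The two extremes need completely opposite selection in the two arms. They are bounds for the assumed 5%, not forecasts.

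**5. Illustration with no true effect (exclusion from analysis)**

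Assume 0.65 in both arms, 180 against 180, and a fraction f excluded from the HGMX side only, with response rate r among those excluded.

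- Remaining HGMX rate: p′ = (0.65 − f·r)/(1 − f). Spurious difference: d = p′ − 0.65.
- Standard error: √[p′(1 − p′)/(180(1 − f)) + 0.65 × 0.35/180].
- Two-sided rejection: 1 − Φ(1.96 − d/SE) + Φ(−1.96 − d/SE).

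Example with f = 0.05 and r = 0: p′ = 0.65/0.95 = 0.684, d = +3.4 points, rejection about 10.5%.

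| r among excluded | f = 2% | f = 5% | f = 10% |
|---|---|---|---|
| 0 | +1.3 points, 5.8% | +3.4 points, 10.5% | +7.2 points, 30.3% |
| 0.30 | +0.7 points, 5.2% | +1.8 points, 6.5% | +3.9 points, 11.9% |
| 0.65 | 0, 5.0% | 0, 5.0% | 0, 5.0% |
| 1.00 | −0.7 points, 5.2% | −1.8 points, 6.5% | −3.9 points, 11.5% |

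The sign and size depend wholly on who is unblinded, which the article cannot tell us.

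**The case against.** The strongest defence is that the two rules need not collide. Section 2.7 makes patients with low intake or prohibited drugs discontinue the trial, while section 2.10 still counts them by intention to treat. Exclusion for violated blinding could work in the same way. The article is also condensed, and the full protocol may define the sets. This stands in part: a reader might infer that the two rules can never both be followed, but that holds only if the exclusion is from the analysis, which section 2.3 does not say. The defence does not remove the point, because the follow-up reading still costs data that could have been collected, and the article as written does not choose between the readings.

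Other stronger readings also go beyond the text.

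- *Patients with serious events would drop out of the safety comparison.* A reader might infer this because section 2.8 says that after an SAE "data for the corresponding participant will be unblinded". But section 2.3 excepts severe AEs from the blinding requirement, so such unblinding is authorised and not plainly a violation, and the safety population in 2.10 has no exception for it.
- *The products can be told apart.* The article calls the differences minor and hard to differentiate, and no patient is scheduled to receive both products. A patient's guess is also not clearly a violation. A link between unblinding and arm or response is a reasonable inference, not a documented fact.
- *Open-label rabeprazole belongs to the same fault.* Section 2.3 does say "but the administration of rabeprazole will be open-label", but that has no bearing on excluding unblinded patients. It is a separate matter, and the Discussion discloses the lack of a rabeprazole placebo as a limitation.

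**Conclusion.** The point holds in this form: section 2.3 fixes an exclusion without an object. One reading contradicts the intention-to-treat rule, another causes avoidable missing data, and no section limits the exclusion to the per-protocol set. This conclusion rests on the wording alone and needs no assumed rate.

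The size of any distortion is unknown. The 15.8 to 26.3 point range depends on an assumed 5% exclusion per arm with opposite extreme selection. The inflated rejection rates depend on exclusions from one side only and on the response rates assumed among those excluded. If patients excluded from analysis respond like everyone else in their arm, no bias is expected. The rule should be settled before treatment codes are opened for analysis, because afterwards any choice could appear to depend on the result.

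**What to change.** Replace the exclusion sentence in section 2.3 with a rule that:

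- records each blinding violation with its date and reason;
- keeps the patient in follow-up and in the intention-to-treat and safety sets;
- confines any exclusion to the per-protocol analysis or a separate sensitivity analysis;
- states that authorised unblinding for a severe AE does not trigger exclusion.

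Sections 2.7 and 2.10 should then agree with it. Whether such a patient continues trial treatment is a clinical matter outside this point.

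The cost is one replaced sentence and one sensitivity analysis. The sample size stays 360, with 180 on HGMX and 180 on placebo.

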**Figure 1 F1:**
[figure not shown]
Study flow diagram. HGMX = Hou Gu Mi Xi.

### Interventions and co-interventions

2.4

#### Standard treatment period (weeks 1 to 2)

2.4.1

All eligible patients will receive standard Western treatment. Specifically, all patients will receive 20 mg rabeprazole b.i.d. and bismuth potassium citrate 0.3 g b.i.d. for 2 weeks. *H pylori*-positive patients will also receive 1 mg amoxicillin b.i.d. and 0.1 g furazolidone b.i.d. for 2 weeks to eradicate *H pylori*.

#### Maintenance treatment period (weeks 3 to 6)

2.4.2

The patients in the 4 groups will receive the following intervention for 4 weeks as maintenance treatment to further facilitate ulcer healing.

1.Group A: HGMX 30 g b.i.d.2.Group B: HGMX placebo 30 g b.i.d.3.Group C: HGMX 30 g b.i.d. + rabeprazole 10 mg q.d.4.Group D: HGMX placebo 30 g b.i.d. + rabeprazole 10 mg q.d.

HGMX is an oatmeal-like solid food (eaten dry or mixed with a liquid) that contains 10.1 g dietary herb material per 30 g. Table 1 presents the components of HGMX in detail. Compared with HGMX, the placebo looks the same (such as label, color and mass) but has minor differences in taste and smell that are hard to differentiate. HGMX and placebo are produced by Jiangzhong Pharmaceutical (group) Co., Ltd., and rabeprazole is produced by Shanghai Xinyi Pharmaceutical Corp. Ltd.

